## Abstract

**Background:**

Medical errors and preventable adverse events are a major cause of concern, especially in the emergency department (ED) where its prevalence has been reported to be roughly of 5–10 % of visits. Due to a short length of stay, emergency patients are often managed by a sole physician – in contrast with other specialties where they can benefit from multiples handover, ward rounds and staff meetings. As some studies report that the rate and severity of errors may decrease when there is more than one physician involved in the management in different settings, we sought to assess the impact of regular systematic cross-checkings between physicians in the ED.

**Design:**

The CHARMED (Cross-checking to reduce adverse events resulting from medical errors in the emergency department) study is a multicenter cluster randomized study that aim to evaluate the reduction of the rate of severe medical errors with implementation of systematic cross checkings between emergency physician, compared to a control period with usual care. This study will evaluate the effect of this intervention on the rate of severe medical errors (i.e. preventable adverse events or near miss) using a previously described two-level chart abstraction. We made the hypothesis that implementing frequent and systematic cross checking will reduce the rate of severe medical errors from 10 to 6 % - 1584 patients will be included, 140 for each period in each center.

**Discussion:**

The CHARMED study will be the largest study that analyse unselected ED charts for medical errors. This could provide evidence that frequent systematic cross-checking will reduce the incidence of severe medical errors.

**Trial registration:**

Clinical Trials, NCT02356926

**Electronic supplementary material:**

The online version of this article (doi:10.1186/s12873-015-0046-1) contains supplementary material, which is available to authorized users.

## Background

Medical errors are a major cause of morbidity and mortality and have been a topic of serious concern [1] since “To err is human” was published by the Institute of Medicine 1999. In the United States, medical errors are thought to be responsible of 100,000 deaths per year and more than one million injuries [1]. In France, 10 000 deaths and up to 3 % of all hospitalizations may be associated with medical errors [2]. For more than a decade, the rate of harm caused by medical errors has remained constant [3], although it is thought that more than a third of them could have been avoided [2, 4].

Emergency Departments (EDs) are busy places, where rapid decisions are made on the basis of incomplete information. Simultaneous management of multiple complex patients and lack of continuity of care can increase the likelihood of medical errors. Conditions in EDs replicate these risks for making medical errors and may amplify their consequences. Rising ED attendance rates in western countries, and subsequent ED overcrowding compounds the situation and further increases the risk of medical errors [5–8]. For these reasons, EDs are considered one of the most high risk environments for adverse events (AE) and serious AE resulting from medical errors. There are sparse data on the rate and severity of AE in the ED. Most previous studies have included passive or self-reporting method for error detection, which is associated with an underestimation of harm and frequency of medical errors. Reported rates of medical errors in the ED vary from 18 [9] to 32 % [10].

Recently, a large prospective study reported that severe medical errors (with the potential to provoke harm) occurred in 10 % of visits in the ED [4] in the US. In France, we conducted a preliminary study, for ED patients that were subsequently admitted, that corroborated these findings, with a medical error rate of 42 %, and an AE rate of 10 % [11].

### Study rationale

Due to the patient’s short length of stay, ED physicians often make independent management decisions. This is in contrast to other specialties, which may benefit from ward rounds, staff meetings, and handover. In our previous study [11], the single protective factor we found, i.e reducing the risk of AE, was the participation of more than one physician in the ED management. This included either the involvement of a resident or trainee in the patient care in addition to the senior physician, or a handover of the patient case in the ED. Recently, Kajdacsy-Balla Amaral et al. reported that night time cross coverage in intensive care unit (ICU) was associated with a significant decrease in mortality [12], with an odds ratio of 0.77 per 1 day of cross coverage. Interestingly, these findings are consistent with high-risk industrial settings, such as aviation setting, where every important decision, calculation or action needs to be cross checked by a peer. These high risk industries have a global mortality rate less than 1 per 100,000.

All these results question the time-honoured paradigm that associates handover and the involvement of more than one decision maker in the process of care with worse outcomes. To explain this, we aim to evaluate the influence of crosschecking physician decision and management in the ED with a peer. Our hypothesis is that the implementation of a systematic and frequent crosschecking within the ED between colleagues decreases the rate of medical errors and AE.

Cross checking may be a rapid and easy intervention to implement even in an overcrowded ED. Thus, this study will also report the feasibility of the implementation of systematic Cross Checking in the ED. We intend to include large numbers of centres in France, that treat diverse patient populations. Consequently, if our hypothesis is confirmed, this will confer a strong argument for future generalization of our intervention .

## Methods

### Study design

The CHARMED study is a prospective, multicenter, cluster-randomized cross-over study in six EDs in France (NCT02356926). Centers will be randomly assigned to use routine management or systematic cross checking in the first period, and will use the alternative strategy in the second period (Fig. 1). Patients will be recruited in six centers in France. Our institutional review board (Comité de protection des personnes - Paris Ile de France 6) authorized the study without the need of signed informed consent as the study.

**Fig. 1 Fig1:**
[figure not shown]
CHARMED study design for period allocation and detection of SME. ED: Emergency Department, SME: severe medical errors, AE: adverse event

### Selection of patients

All patients that visit the ED during one of the two periods of recruitment, Monday to Friday between 8:30 am and 4:30 pm, will be screened for inclusion. We chose this time interval as they correspond to period that can be exposed to a cross checking, which will occur at 11:30 am, 2:00 pm and 4:30 pm. Patients with the following will be excluded:Patients whose care is not provided by an EP (for example psychiatrist or maxillo-facial surgeon)Scheduled return attendance to the EDLow severity, defined byTriage level 5 on a 1 to 5 scale (5 being the less severe) [13, 14]Patients referred to a “minor” or “fast track” unitPatients discharged home less than 1 h after first contact with an EP

After the completion of the two study periods, a clinician research technician (CRT) will electronically retrieve the list of patients that attended the ED during the recruiting period. Each center has electronic software that records all admission with the time of arrival and time of discharge. All patients that entered or left the ED within the recruitment period (i.e. Monday to Friday, 9 am to 5 pm, over a specified 2 week period) will be retrieved by their semi-anonymised number, hospital identification number), and the CRT will verify that they have no exclusion criteria. The independent methodology and research department will then randomly select 14 attendances for each of the 10 days of enrollment per period, for a total of 280 visits in each centre.

### Definition of key term and endpoints

In accordance to national and international recommendations [1, 2, 15], the following definitions will be used:**Medical Error**: Failure of a planned action to be completed as intended, or the use of a wrong plan to achieve an aim. The severity of an error will be classified using the National Coordinating Council on Medical Error and Reporting (NCCMERP) from A to I [16], as shown in Table 1.**Adverse event (AE)**: An injury that might have resulted from medical care (or lack thereof).**Near Miss**: A medical error that has the potential to cause an adverse event, but did not either by chance or after an intervention. A near miss is an error of severity B, C or D.**Preventable AE**: An AE associated with an error. A preventable AE is a medical error of severity E, F, G, H or I.**Severe Medical Error (SME)**: preventable AE or a near miss.

**Table 1 Tab1:** National Coordinating Council for Medication Errors Reporting and Prevention (NCCMERP) classification of severity of medical errors

A	Circumstances or events that have the capacity to cause error
B	An error occurred but the error did not reach the patient
C	An error occurred that reached the patient but did not cause patient harm
D	An error occurred that reached the patient and required monitoring to confirm that it resulted in no harm and/or required intervention to preclude harm
E	An error occurred that may have contributed to or resulted in temporary harm
F	An error occurred that may have contributed to or resulted in temporary harm and required initial or prolonged hospitalization
G	An error occurred that may have contributed to or resulted in permanent patient harm
H	An error occurred that required intervention necessary to sustain life
I	An error occurred that may have contributed to or resulted in the patient’s death

The primary objective is to assess whether the implementation of Systematic Cross Checking in the ED will reduce the rate of severe medical errors. The primary endpoint is the rate of SME in the seven days following ED visits. Serious guidelines violation (local or national), even in the absence of any documented injury, will be considered as adverse events - As previously described, the subsequent adverse events might not clearly appear in the ED settings, hence its classification as a SME [8]. Hospital or ED re-attendance within the next 7 days will be also considered as an adverse event.

Secondary endpoints include the followings:Rate of AE and preventable AERate of Near MissSeverity of SMEFactors associated to SME:o Related to patient (age, chief complaint, comorbidities, triage level)o Related to physician (grade, experience, number of physician involved, handoff)o Related to the ED visit (Time of visit, daily occupancy, crowding, waiting time, length of stay, total number of emergency physicians)

### Experimental plan

In both periods, from 9am to 5pm, a CRT will be present in the ED to collect variables on providers and patients.

**In the control period**, usual care and routine management will be provided.

**In the intervention group**, systematic cross-checking will be implemented three times a day from 8:30 am to 6:00 pm between emergency physicians. The CRT will seek emergency physicians (EP) by pairs for crosschecking. Senior physicians will use peer crosschecking (i.e. crosschecker will also be an emergency senior physician). The CRT will assist the pairing. Each EP will present all his or her current patients. Patient presentation will be semi protocolised (see below), although usual presentation will be sought as this is the presentation method already in place for handover. The crosschecking will occur in the presence of the CRT and in the ED, in any medical office staff room, or cubicle available.

Each EP will then have to present the patients he is actually taking care of, with brief description of the case including the following items:Sex, age, chief complaint and main medical historyMain clinical findingsMain investigation (laboratory and imaging) results available/outstandingTreatment given in the EDBrief summary of the plan (suspected diagnosis, discharge/admission)

The CRT will pass a written copy of this plan of cross checking to each EP. After a case has been presented by the EP, the comments and advice of the crosschecker will be sought. Examples of Cross Checking sessions are provided in Table 2

**Table 2 Tab2:** Examples of cross checking

*Example 1:*
*EP1: I am seeing a 32 year old male, with acute flank pain and history of renal colic.*
*No fever and no guarding, right lumbar excruciating pain. Urinary dipstick is positive for blood. He’s been pain free since we gave him Ibuprofen. I am awaiting his electrolytes results and if normal, will discharge him with outpatient CT scan in the next week and analgesia.*
*EP2: OK. Next patient?*
*Example 2:*
*EP 1: I am seeing a 65 woman with shortness of breath and history of COPD, it is likely Exacerbation of COPD. PH is normal, bicarb 30, no elevated lactate. If the chest X-ray is normal then I will admit her to the ward for a course of nebulizers as she is still dyspneic.*
*EP2 : What are her clinical findings. Have you started any treatment yet?*
*EP 1: She is 140/58, pulse 101, temperature 38.2 °C. I have her on Salbutamol nebulizer.*
*EP 2: Ok. Shouldn’t you consider starting an antibiotics course and prednisolone?*

### Chart review and adjudication of endpoints

First, the local investigator in each center will review charts from his or her center, as detailed below. The local investigator will undergo formal training by the study coordinator including a 60 min training session by telephone; live slides presentation; and practice chart reviews with feedback. This method of training has been used in a previous study by Camargo et al. and is detailed in his previous publications [4, 17]. For all selected patients, a CRT will retrieve the complete medical chart pertaining to the ED visit, and if the patient was admitted into hospital, discharge summaries following hospital discharge. Repeat attendance in the ED within the next 7 days will be recorded. All charts will be blinded to date, period and group. Chart review for SME will then be assessed in a validated two phase review process [3, 4, 17–21] (Fig. 1).

This first chart review phase will use a an adapted validated questionnaire, derived from the NEDSS study [17], as a screen to detect adverse events and near misses (Additional file 1). Any chart that screens positive for at least one item at the first review phase will be sent for external validation and confirmation in the second review phase. These screen-positive charts will be centralized at the methodology and research department and will be independently reviewed by two physicians from a review expert panel in the second chart review phase. This panel will include board-certified emergency physicians and experts in patient safety. Some of the panel members are already trained to chart abstraction and errors validation and classification [11]. The others from the panel will complete a specific training session, with practice chart review and presentation of classification of error in their severity (according to NCCMERP). In cases of disagreement after discussion with the paired reviewer and failure to reach consensus, a third expert, faculty member emergency physician, will be sought to make a final decision. The preventability of any potential adverse event will be reported on a Likert scale as follows: 0) highly unlikely 1) unlikely 2) likely 3) highly likely.

This two-level reviewing system has been widely used in previous studies on medical errors [3, 18–23], although rarely in the ED setting [17]. To evaluate whether the first level is reliable, we will randomly select 100 charts that were initially screened negative on the first level, and send them for external reviewing. If the rate of SME is higher than 2 % (i.e. upper 95 % confidence interval (CI) bound > 5 %), all charts will undergo the second level of reviewing to limit selection bias.

### Statistical analysis

Patient characteristics will be reported in each period, and we will calculate number (rate), mean (standard deviation) or median (interquartile range) when appropriate. Normality will be tested with Kolmogorov-Smirnov method. Proportion of SME will be expressed as percentage and its exact 95 % CI. Characteristics of the two periods will be compared, and differences in any of the following variables will be sought: characteristics of patients and physicians, daily census and severity of patients (triage level, admission rate and ICU admission rate).

The effect of cross-checking will be estimated through a generalized estimating equation (GEE) model, which will take into account the independence of intracluster observations. Factors associated with SME will also be sought with a GEE Model. Severity of SME will be described and compared between the two periods with a chi square test or Fisher exact test when appropriate.

Based on previous literature, we estimate a rate of SME of 10 %, with a potential avoidance rate of more than 50 % [4, 11, 24]. With a hypothesis of a 40 % reduction in the rate of SME (10 % control vs 6 % cross checking), with alpha = 0.05 and beta = 0.2 and accounting for the fact that the cross-over will counterbalance the cluster’s inflation factor, we need to analyze 1584 charts – 140 per period in each center.

All statistical tests will be two-tailed, and a p less than 0.05 will be required to reject the null hypothesis.

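### The primary analysis is a GEE on six centres, described as handling independence instead of correlation; by default its two-sided error would be about 13% (18% with a period term)

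*Protocol article*

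**What the plan says.** Study design describes a "prospective, multicenter, cluster-randomized cross-over study in six EDs in France". Each centre starts with one strategy and "will use the alternative strategy in the second period". The randomised units are therefore the six centres, each observed under both strategies.

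Selection of patients fixes the charts: the research department will "randomly select 14 attendances for each of the 10 days of enrollment per period, for a total of 280 visits in each centre". That is 140 per centre and period.

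Statistical analysis names the method: "The effect of cross-checking will be estimated through a generalized estimating equation (GEE) model, which will take into account the independence of intracluster observations". On the decision rule it says: "All statistical tests will be two-tailed, and a p less than 0.05 will be required to reject the null hypothesis". The sample size assumes "10 % control vs 6 % cross checking" "with alpha = 0.05 and beta = 0.2". It arrives at 1584 charts on the stated ground that the cross-over offsets the inflation due to clustering, and it gives no intracluster correlation.

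The article does not give the type of standard error, the working correlation, the covariates, the reference distribution or any small-sample correction.

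**The concern.** Two things are fixed in the text and fit badly together.

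First, the only sentence on how clustering enters the primary analysis says that the model handles independence within clusters. Visits to the same centre share staff, case mix and local practice, so correlation is what the model has to handle.

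Second, the method is a GEE and there are six clusters. The usual GEE test divides the estimate by a sandwich standard error and compares the ratio with 1.96. Both steps are large-sample approximations in the number of clusters. With six, the sandwich variance is too small on average, and the normal reference ignores that it is estimated from only four or five degrees of freedom.

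At stake is the trial's one primary comparison. Under the default test, a benefit of cross-checking would be declared too often when there is none, and the confidence interval would be too narrow.

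**Working it through.** **Inputs.** From the article: 6 centres, 2 periods, 140 charts per cell, 10% against 6%, two-sided alpha 0.05, power 80%. Assumed, because the article does not give them: three centres per sequence, and between-centre and centre-by-period variation on the logit scale as stated below.

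**The plan's own sample size.** The ordinary two-proportion formula for 10% against 6% gives 721 per group, 1442 in all. With a continuity correction it gives 1542. The stated 1584 lies within 3% of 1542, and 1442 plus 10% is about 1587. So 1584 is close to a calculation that treats charts as independent. With 792 per group that calculation has 83.6% power. (12 cells of 140 make 1680, not 1584; that is a separate matter.)

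**Size of the default test.** In a balanced cross-over the treatment effect is estimated from the six within-centre differences. An uncorrected sandwich divides their residual sum of squares by 6, where the valid estimate divides by the degrees of freedom (df): 5 with no period term, 4 with one. Hence z = t × √(6/df), and the real size is P(|t_df| > 1.96 × √(df/6)).

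- No period term: P(|t₅| > 1.96 × √(5/6)) = P(|t₅| > 1.789) = 13.4%.
- Period term: P(|t₄| > 1.96 × √(4/6)) = P(|t₄| > 1.600) = 18.5%.

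**Simulation check.** Logit GEE, 6 centres × 2 periods × 140 charts, 10% error rate under the null, 4,000 runs per setting, centre SD 0 to 0.33, centre-by-period SD 0 to 0.2, independence and exchangeable working correlation. With no true period effect:

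| Test | Two-sided size |
|---|---|
| Uncorrected sandwich, normal reference, no period term | 13.0–14.6% |
| Uncorrected sandwich, normal reference, period term | 18.0–19.9% |
| Variance scaled by 6/5, t on 5 df, no period term | 4.6–5.6% |
| Variance scaled by 6/4, t on 4 df, period term | 4.4–5.6% |

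**With a true period effect and no period term**, the uncorrected test becomes less liberal: 11.5% and 5.2% at log odds ratios of 0.2 and 0.4 (centre-by-period SD 0.2), and 6.1% and 1.5% at 0.3 and 0.5 (SD 0).

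**Model-based standard errors** (exchangeable, period term, normal reference) give about 5% with no centre-by-period variation and 11–13% when its SD is 0.2.

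**Width of a valid interval relative to the uncorrected one.**

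- 5 df: (2.571/1.960) × √(6/5) = 1.44.
- 4 df: (2.776/1.960) × √(6/4) = 1.73.

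**Power of a valid test, best case** (no centre-by-period variation, the same rates in every centre). SE = √[(0.10 × 0.90 + 0.06 × 0.94)/(140 × 6)] = 0.0132, so the non-centrality is 0.04/0.0132 = 3.03. The non-central t distribution gives 68% on 5 df and 63% on 4 df. With 132 charts per cell (1584/12) it gives 66% and 60%.

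**The case against.** The strongest reply is that the inflation is read from silence. The article says GEE and no more. A condensed article may leave the variance estimator, the period term and a small-sample correction to the analysis plan, which is not shown. This stands, and it limits the point to a conditional one. A reader might infer that 13% to 18% is the trial's real error rate. The documents do not support that, because a corrected test would have about 5%, and so might a model-based one if centres do not vary between periods.

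A reader might also infer that a missing period term causes the inflation. It does not. The article neither includes nor excludes one. The 18% arises only when the term is included without correction, and leaving out a real period effect makes the test less liberal or even conservative.

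A third tempting step concerns the secondary analysis: "Factors associated with SME will also be sought with a GEE Model". A sandwich matrix from six clusters has rank at most six, fewer than the candidate factors listed under the secondary endpoints. But the article does not say that all of them enter one model, so this does not follow.

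Finally, independence is probably a slip for non-independence, since choosing a GEE shows the intent. That is likely, but the sentence is still wrong and needs correcting.

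What the reply does not remove is that the method and the number of clusters are both fixed in the text, and the method's usual form fails at that number.

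**Conclusion.** The point holds in conditional form. The article commits the primary comparison to a GEE on six randomised centres and misdescribes the dependence that the model must handle. If the usual uncorrected sandwich and normal reference are used, and there is no true period effect, the two-sided error rate is about 13%, or about 18% with a period term, against the stated 5%. That is 2.7 to 3.7 times nominal (13.4/5 and 18.5/5).

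The figures assume three centres per sequence and 140 charts per cell. The closed form does not depend on the intracluster correlation, and the simulation agrees over the range tried. If the analysis plan already fixes a small-sample method, what remains is the wrong word and the power statement: a test that respects six centres reaches about 63% to 68% in the best case, not 80%.

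**What to change.** In Statistical analysis, replace independence with correlation, and specify one of the following before unblinding:

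1. A GEE with treatment and period terms, a small-sample corrected sandwich variance (for example Kauermann-Carroll or Fay-Graubard) and a t reference on 4 df.
2. An analysis of the six within-centre differences in the proportion with a severe medical error, adjusted for period and tested against t on 4 df.

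Both assume that the two sequences are each used, which the article should state. The two are alternatives and need not give identical results, so one should be named as primary. The simulation above tested simple degrees-of-freedom scaling with a t reference, not the two named corrections.

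If the analysis plan already contains such a method, confirm it and correct the sentence.

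The change needs no new data, but it has a cost. The interval is about 1.4 times (5 df, no period term) to 1.7 times (4 df, period term) as wide as the uncorrected one. The power statement should be redone for the chosen test: at 10% against 6% with 140 charts per cell and no centre-by-period variation, it is about 63% on 4 df (68% on 5 df), and lower if centres vary between periods.

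### With six EDs as clusters, the usual robust GEE tests for factors associated with SME are anti-conservative, and length of stay may be partly a consequence of the error

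*Protocol article*

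**What the plan says.** The design is a "cluster-randomized cross-over study in six EDs in France" (Study design). Factors associated with SME are a secondary endpoint, listed under Definition of key term and endpoints in three groups:

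- Patient, four factors: "Related to patient (age, chief complaint, comorbidities, triage level".
- Physician, four factors: "Related to physician (grade, experience, number of physician involved, handoff".
- Visit, six factors: "Time of visit, daily occupancy, crowding, waiting time, length of stay, total number of emergency physicians".

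The Statistical analysis section gives the method in one sentence: "Factors associated with SME will also be sought with a GEE Model". It also sets a two-sided 5% threshold for all tests. The article does not say whether the factors enter one model or several, which variance estimator is used, or which reference distribution applies.

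Table 1 describes severity grade D as an error that reached the patient and "required monitoring to confirm that it resulted in no harm", or that needed intervention to prevent harm. Grade D is a near miss and therefore counts as an SME.

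**The concern.** Two separate matters arise.

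First, GEE inference is normally based on a robust (sandwich) variance, whose validity depends on the number of clusters. Here there are six. Two listed factors, triage level and chief complaint, have several categories and need joint tests, and joint tests suffer most when clusters are few.

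Second, length of stay is listed as an explanatory factor for SME, but it is measured over the visit in which the error occurs. An error that leads to extra monitoring or intervention can lengthen that visit. The association may then run from error to stay. In a joint model, adjusting for length of stay may also distort the estimates of factors that act through it, such as crowding.

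What is at stake is a secondary endpoint whose results may guide later interventions. The Study rationale shows how this can happen: a factor found protective in the group's previous study is part of the reason for this trial.

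**Working it through.** **Inputs from the protocol article.** Six EDs. Fourteen factors (4 + 4 + 6). Triage levels 1–4 remain because level 5 is excluded, so triage has 3 df. SME rates are "10 % control vs 6 % cross checking", a mean of 8%.

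**Assumptions.** Centre SD of 0.3 on the logit scale; chief complaint in 4, 6 or 8 classes; every factor null and varying from chart to chart; independence working correlation.

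**The plan's own figure.** No figure is given for the factor analysis; sample size enters only through the number of events. The continuity-corrected formula for 10% against 6% gives 771 per arm, or 1542 in total, 2.7% below the stated 1584. The article's 140 charts per period and centre give 140 × 2 × 6 = 1680. Expected SMEs are therefore 0.08 × 1584 = 127 to 0.08 × 1680 = 134.

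**Rank.** The middle of the sandwich is built from six centre score vectors that sum to zero, so its rank is at most 5. It was 5 in every simulated fit, for models with 19 to 23 parameters. A joint robust test with six or more df is therefore undefined.

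**Theory.** For q coefficients and six clusters, the statistic behaves approximately as T² = [5q/(6−q)] × F(q, 6−q). If it is compared with the chi-square cut-off c, the false-positive rate is P{F(q, 6−q) > c(6−q)/(5q)}. A sandwich that divides by 6 rather than 5 inflates the statistic by 6/5, which multiplies that threshold by 5/6.

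| q | c | Threshold | Rate | Threshold × 5/6 | Rate |
|---|---|---|---|---|---|
| 1 | 3.84 | 3.84 | 11% | 3.20 | 13% |
| 3 | 7.81 | 1.56 | 36% | 1.30 | 42% |
| 5 | 11.07 | 0.443 | 81% | 0.369 | 84% |

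**Simulation.** Six centres of 280 charts, SME 10% and 6%, uncorrected sandwich.

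| Test | All factors in one model | One factor at a time | Joint model, model-based variance |
|---|---|---|---|
| One coefficient | 14% | 15% | 5% |
| Triage, 3 df | 38–40% | 41% | 4–6% |
| Chief complaint, 4 classes (3 df) | 43% | not run | 6% |
| Chief complaint, 6 classes (5 df) | 85% | 84% | 4% |

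A second simulation with 264 charts per centre gave 44% for triage and 84% for a 5-df chief complaint. A further check gave 12% for one coefficient and 43% for triage. With eight classes (7 df) the robust covariance block is singular; a pseudo-inverse returns a rejection rate of 46%, but this is not a valid test.

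The single-factor and joint columns agree, so the inflation comes from the six clusters and not from the number of factors.

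**Alternatives on the same type of data.** An F(q, 6−q) reference gives about 6%. Logistic regression with centre as a fixed effect and likelihood-ratio tests gives about 5–6%.

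**Length of stay.** Assume that it has no effect on SME and that an SME lengthens it by a given number of SDs.

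| Shift (SD) | Flagged, sandwich | Flagged, model-based |
|---|---|---|
| 0 | 15% | 5% |
| 0.1 | 29% | 18% |
| 0.2 | 72% | 62% |
| 0.3 | 90% | 89% |
| 0.5 | 100% | 100% |

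Only the first row is a type I error. The other rows are detections of an association that exists but runs in the opposite direction.

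**The case against.** The strongest reply is that the article is condensed. It names a GEE but not the variance estimator, any correction or the reference distribution, and such details commonly sit in an analysis plan that is not shown. With model-based variance the same tests reject at 3–6%. This stands. The inflation is conditional on the usual default, and the missing detail is not itself a fault. What can be criticised is the stated combination of a GEE, six clusters, multi-category factors and a 5% threshold, for which the default is unsafe.

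Four stronger readings are tempting, and the documents do not support them.

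- *The model must carry all 14 factors, and that causes the problem.* The article does not say they enter one model, and single-factor models show the same inflation.
- *Triage and chief complaint will be declared whatever the truth.* Even with the uncorrected sandwich, triage is falsely declared in fewer than half of null trials, and the 5-df figure rests on an assumed grouping.
- *Errors prolong the stay.* The documents give no figure. Grade D makes it plausible. Grade F concerns hospitalisation rather than the ED stay, grade B errors never reach the patient, and re-attendance within 7 days falls after the index visit.
- *A flagged length of stay is a false positive.* The plan promises associations, not causes. If errors lengthen the stay, the association is real and only a causal reading would be wrong.

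**Conclusion.** The point holds in a limited form. With the usual centre-level robust variance and a chi-square reference, six clusters give false-positive rates of about 11–15% (1 df), 36–44% (triage, 3 df) and about 80–85% (5 df, assumed grouping), and no joint robust test exists for six or more df. These rates apply only if that default is used. They also rest on the assumed centre SD and on factors that vary from chart to chart; factors shared by all charts of a day, such as daily occupancy, were not examined separately.

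Length of stay may be flagged through reverse direction under any variance estimator. The size is unknown because the shift is an assumption. The matter is confined to a secondary analysis and does not touch the primary comparison.

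**What to change.** For the factor analysis only:

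1. Use logistic regression with centre as a fixed effect, plus allocation and period, and likelihood-ratio tests. Alternatively, keep the GEE but refer the robust tests to the scaled F(q, 6−q) distribution and allow no factor above 5 df. The first option is preferable for multi-category factors. At q = 5 the scaled F has one denominator df and its 5% critical value is about 5754, against 11.07 for chi-square, so that test would have almost no power.
2. Group chief complaint into a few classes fixed in advance, in view of 127–134 expected events. Centre, allocation and period already use 5 + 1 + 1 = 7 coefficients.
3. Take length of stay out of the multivariable explanatory model and report it descriptively by SME status, as a possible consequence of the error.

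The change is to the analysis wording and needs no new data. The cost is coarser chief-complaint classes and no adjusted estimate for length of stay.
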